### Plan of investigation

The study will have a cohort design. We will follow up a cohort of patients systematically selected from each trust. For pragmatic purposes we will sample all patients who are admitted every third month, starting from October 2009. Over one calendar month, there will be ~ 300-350 stroke cases entered into the Network Clinical Data. Between October 2009 and September 2011, the Clinical Network would have collected a total of eight 3-monthly datasets per trust (i.e. 8 study months in total: Oct 2009, Jan 2010, April 2010, July 2010, October 2010, Jan 2011, April 2011, July 2011). Therefore, the estimated total cohort size with baseline clinical data will be ~ 2,400 stroke cases during this exercise (30% of 4000 patients admitted annually in 8 trusts = 1200 × 2 yrs).

We will collect patient data by hospital trusts and conduct a questionnaire survey of patients' outcomes. Due to the nature of the study we would need 100% follow-up in randomly selected populations. Because we will be using a partially historical cohort, to avoid selection bias for mortality outcome, informed consent from all eligible participants will not be feasible. Therefore, it is most appropriate for the clinical team to collect the outcome data to comply with current ethical guidance in the UK. Therefore, the identifiable patient data will only be held at the local NHS trusts.

Neither the network nor the investigators will have access to any identifiable patient information (e.g. name, address). For outcome data we will utilise death certificate and hospital episode data from the Patient Administrative System (PAS) as described previously [14,15]. This approach will be used in conjunction with telephone and postal follow-up for questionnaire surveys such as EQ-5 D, and Stroke Impact Scale. These data will be counter-checked using discharge coding records, which record each hospital episode.

The clinical teams will retrieve case records to collect (1) baseline measures which were not recorded in baseline Network surveys and (2) outcome measures including mortality and hospital length of stay. At study commencement (October 2010) one year follow up data can be collected immediately for October 2009 cohorts (follow up complete at end September 2010). The follow up will be completed in September 2012 as the stroke patients included in the last survey for the study conducted by the Network in July 2011 will complete one year follow-up in June 2012 and data collection of the study will be completed by July-August 2012 with the view of final cohort data arrival to research team by the end of December 2012.

Due to multi-centre nature of the study the individual sites are expected to join the study at different time points (after their respective NHS Research & Development Committees' approval). We will collect characteristics of stroke services, patient related factors, prognostic indicators, treatment options and trial/study participation. Missing prognostic data will be imputed statistically, to ensure that all eligible patients are included in the primary analysis (see also Statistical Methods).

The service characteristics of interest include:

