**Methods/Design:**

We will conduct a cohort study in eight acute NHS trusts within East of England, with at least one year of follow-up after stroke. The study population will be a systematically selected representative sample of patients admitted with stroke during the study period, recruited within each hospital. We will collect individual patient data on prognostic characteristics, health care received, outcomes and costs of care and we will also record relevant characteristics of each provider organisation. The determinants of one year outcome including patient reported outcome will be assessed statistically with proportional hazards regression models. Self (or proxy) completed EuroQol (EQ-5D) questionnaires will measure quality of life at baseline and follow-up for cost utility analyses.

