### Sample size

Since this is an exploratory study designed to provide information for further analytic research, sample size will be determined partly pragmatically rather than on particular hypothesis tests. For illustration purposes, a total sample of 2264 patients would provide 80% power to detect a constant Hazard ratio (HR) of 0.76 for one-year mortality between two groups of roughly equal size, based on the log-rank test. This assumes a 20% one-year mortality rate in the reference group, no loss to follow-up before one year and 2-sided type I error of 5%. If one-year mortality is 30%, then 2264 patients would provide 76% power to detect a HR of 0.81.

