### Outcome measurements

Primary outcome of the study will be one year mortality comparison between services with different characteristics. The secondary outcomes will include (1) final discharge destination (good or poor outcome) [16], (2) length of acute hospital stay, (3) length of stay in rehabilitation, (4) complications during acute and rehab-hospital stay and significant procedures (e.g. aspiration pneumonia, myocardial infarction), (5) readmissions, (6) composite cardiovascular events (recurrent TIA/Stroke/Acute Coronary Syndrome, Myocardial infarction).

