#### Outcome

As the National Institute of Health and Clinical Excellence [18] recommends use of the EQ-5 D [17] within cost-effectiveness analysis this will be our primary measure within the economic analyses. EQ-5 D data will be collected at two University Hospitals and two district general hospitals within the clinical network. We will use "mapping" strategy to estimate the cost-effectiveness analyses across the region. The use of mapping, where scores from a condition-specific (non preference-based) measure are 'converted' into a utility (preference-based) score using a pre-defined formulae, has been advocated (in certain instances) by the UK National Institute of Health and Clinical Excellence (NICE) [18], and has been used to estimate the utility scores, and in turn cost-effectiveness, of a number of health care interventions [19]. Mapping presents the possibility of not asking all participants to complete the EQ-5 D. In this study we propose to take advantage of this by developing a mapping algorithm based on the response from participants participating in this component to predict the EQ-5 D for participants in retrospective cohorts and those who did not participate in PROM component.

Because the quality of life measure (EQ-5D) which can be used to estimate health utility and calculate QALYs (Quality Adjusted Life Years) for economic evaluation is outside the remit of routine data collection and cannot be done retrospectively, we will collect EQ-5 D data in only the second year of the study (October 2010 and January, April and July 2011 cohorts and one year follow up data to be collected September and December 2011, and March and June 2012) in those who provide informed consent to the study (we estimate that the sample will be approximately 15-20% of the whole sample after excluding the one year pre-study period (between October 2009-September 2010) and after taking into account of refusal rate (estimated ~ 30%) in trusts with Stroke or Comprehensive Local Research Network Research Nurses.

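### The stated one-year completion and EQ-5D collection dates fall in the month before patients' first anniversaries and conflict with the one-year horizon

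*Protocol article*

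**What the plan says.** Recruitment is by whole calendar month: "we will sample all patients who are admitted every third month, starting from October 2009" (Plan of investigation). The Abstract describes a cohort "with at least one year of follow-up after stroke". Outcome measurements states: "Primary outcome of the study will be one year mortality comparison between services with different characteristics". The power illustration under Sample size assumes "no loss to follow-up before one year".

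The dates given for individual cohorts are these:

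- **October 2009 admissions** (Plan of investigation): at study start in October 2010, "one year follow up data can be collected immediately for October 2009 cohorts (follow up complete at end September 2010".
- **July 2011 admissions** (Plan of investigation): these patients "will complete one year follow-up in June 2012 and data collection of the study will be completed by July-August 2012".
- **EQ-5D in the October 2010 and January, April and July 2011 cohorts** (Outcome, under Economic evaluation): "one year follow up data to be collected September and December 2011, and March and June 2012". The Economic evaluation section itself places the follow-up EQ-5D at 12 months.

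The sentence on the July 2011 cohort also gives September 2012 as the end of follow-up, and December 2012 for arrival of the final data with the research team. No end date is given for the January, April and July 2010 cohorts.

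**The concern.** A patient admitted on a given day of October 2009 reaches one year on the same day of October 2010, not by the end of September. Every cohort-specific date in the article shows the same one-month miscount, so this is a pattern and not a slip in one place.

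Three things are at stake.

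1. **EQ-5D timing.** EQ-5D is the effectiveness measure for the economic evaluation, the source of the QALYs and the basis of the mapping algorithm. The article says that it cannot be collected retrospectively, so a questionnaire sent a month early cannot be repaired later.
2. **Early extraction.** Records for October 2009 pulled at once in October 2010 may stop short of one year. Cox regression can censor such patients. The logistic models planned for dichotomised outcomes do not, so any such outcome counted to one year, for example readmission, could be misclassified.
3. **Uneven ascertainment.** Trusts join at different times, and many exposures are hospital characteristics. A trust that extracts at once would have shorter ascertainment than a late joiner. This is a risk, not a demonstrated bias.

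**Working it through.** **1. Follow-up to the end of each stated month** (admission months and end months from Plan of investigation and Outcome; days = end date minus admission date):

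| Admission month | Stated end | Admitted first day | Admitted last day | Mid-range |
|---|---|---|---|---|
| October 2009 | 30 Sep 2010 | 364 | 334 | 349 |
| October 2010 | 30 Sep 2011 | 364 | 334 | 349 |
| January 2011 | 31 Dec 2011 | 364 | 334 | 349 |
| April 2011 | 31 Mar 2012 | 365 | 336 | 350.5 |
| July 2011 | 30 Jun 2012 | 365 | 335 | 350 |

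The shortfall against the calendar anniversary is 1 to 31 days (1 to 30 for April), about 16 on average. February 2012 had 29 days, so the anniversary of an April or July 2011 admission is day 366. A patient admitted on the 1st of those months does reach 365 days.

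**2. EQ-5D timing if collected within the stated month.** The earliest case is the last admission day surveyed on the first day of the collection month; the latest is the first admission day surveyed on its last day.

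- October 2010 cohort, September 2011: 305 to 364 days.
- January 2011 cohort, December 2011: 304 to 364 days.
- April 2011 cohort, March 2012: 306 to 365 days.
- July 2011 cohort, June 2012: 306 to 365 days.

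That is roughly 305 to 365 days, with a midpoint near 335, or about 11 months.

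**3. The plan's own power figures.** Inputs from Sample size: 2264 patients in two roughly equal groups (1132 each), reference mortality 20% with HR 0.76, or 30% with HR 0.81, two-sided 5%. Formulae: events D = 1132 × [(1 − S) + (1 − S^HR)], with S = 1 − reference mortality; power = Φ(½·√D·|ln HR| − 1.96).

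- 20%, HR 0.76: D = 1132 × (0.2000 + 0.1560) = 403; power = Φ(2.755 − 1.96) = 78.7% (plan: 80%).
- 30%, HR 0.81: D = 1132 × (0.3000 + 0.2509) = 624; power = Φ(2.631 − 1.96) = 74.9% (plan: 76%).

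Both figures reproduce within 2 points.

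**4. Worst case for mortality.** Assume that the dates are hard cut-offs for all patients, with mean follow-up of 11.5 months, and that the hazard is constant. Replace S by S^(11.5/12).

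- 20%, HR 0.76: D = 1132 × (0.1925 + 0.1500) = 388; about 15 deaths lost; power 77.1%, a loss of 1.6 points.
- 30%, HR 0.81: D = 1132 × (0.2895 + 0.2418) = 602; about 22 deaths lost; power 73.4%, a loss of 1.5 points.

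If the stated mortality is applied to all 2264 patients with a 16-day shortfall:

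- 20%: 0.20 − (1 − 0.8^(349/365)) = 0.0079, or about 18 of 453 deaths.
- 30%: 0.30 − (1 − 0.7^(349/365)) = 0.0110, or about 25 of 679 deaths.

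If the hazard falls after the first weeks, as it would if deaths cluster early after stroke, the losses are smaller.

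**5. The later completion dates.** Followed to the end of July, August or September 2012, a patient admitted on 31 July 2011 has 366, 397 or 427 days. Any of these three dates covers the whole July 2011 cohort.

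**The case against.** A reader might infer that every patient is followed for only 11 to 12 months and that one-year mortality is therefore undercounted. The document does not support that reading, for four reasons.

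- Nothing states that the cohort dates are cut-offs for ascertaining outcomes. The Abstract promises at least a year, and September 2012, also given as the end of follow-up, lies after the last anniversary of 31 July 2012. The text contradicts itself; it does not fix a shorter horizon.
- Three of the eight cohorts have no stated end date, and the EQ-5D months concern only consenting patients, an estimated 15-20% of the sample.
- Deaths come from death certificates and hospital administrative records, which a later extraction can read up to each anniversary. Collection in October 2010 is described as possible, not required, and sites will join later at different times.
- The primary analysis is of time to death by Cox regression, which accommodates censoring slightly before one year. The power calculation is offered as illustration in an exploratory study.

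All of this stands for mortality. It does not remove the date error. The September 2012 date says nothing about October 2009, and the sentence containing it relies on the mistaken June 2012 date. Nor does any of it help EQ-5D, where the stated months are the collection schedule and a missed time point cannot be recovered. Patients admitted early in a month and surveyed at the end of the collection month would be short by only days, so 11 months is a midpoint and not a fixed value.

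**Conclusion.** The point holds as a systematic date error and an internal contradiction. The completion dates for the October 2009 and July 2011 cohorts, and all four one-year EQ-5D months, precede the first anniversaries of the patients concerned. September 2012 and July-August 2012 are both given as completion, with follow-up apparently ending after data collection.

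The firm consequence, if the schedule is followed, is a one-year EQ-5D taken at roughly 305 to 365 days. The conditional consequence is that October 2009 records extracted at once in October 2010 may be up to a month short. For mortality, the upper bound at 20% is about 15 of 403 expected deaths (18 of 453 if 20% applies to everyone) and about 1.5 points of power. That bound assumes hard cut-offs in all cohorts and a constant hazard, and the protocol states neither for the cohorts as a whole. Bias in the primary comparison between services is not shown.

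**What to change.** - Define follow-up for each patient as running from admission to the first anniversary of admission, and count deaths and other one-year outcomes to that date whenever the records are read.
- Extract each cohort's outcomes only after its last anniversary: from 1 November 2010 for October 2009, through to 1 August 2012 for July 2011. State the corresponding dates for the January, April and July 2010 cohorts.
- Schedule the one-year EQ-5D around each patient's anniversary, in October 2011 and January, April and July 2012, and record the date of completion.
- Give one date for the end of follow-up and a consistent, later date for the end of data collection.

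The cost is a shift of about one month in extraction and questionnaire dates. The last anniversary is 31 July 2012 and final data are due by the end of December 2012, so the existing deadline is unaffected.

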#### At hospital level

• staffing (including junior doctors and therapists (whole time equivalent), physicians characteristics

• university or district general hospital

• distance from tertiary referral centre

• availability of vascular surgery on site, neuro-surgery and neuro ITU on site

• monitoring beds

• physician on call rota

• compliance with NICE guidelines

#### At patient level

• provision of thrombolysis and CT

• medication

### Outcome measurements

Primary outcome of the study will be one year mortality comparison between services with different characteristics. The secondary outcomes will include (1) final discharge destination (good or poor outcome) [16], (2) length of acute hospital stay, (3) length of stay in rehabilitation, (4) complications during acute and rehab-hospital stay and significant procedures (e.g. aspiration pneumonia, myocardial infarction), (5) readmissions, (6) composite cardiovascular events (recurrent TIA/Stroke/Acute Coronary Syndrome, Myocardial infarction).

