## Background

Stroke is the third leading cause of mortality and the number one cause of long-term disability in the UK. More than 150,000 people suffer a stroke in the UK each year [1]. It costs the NHS approximately £ 7 billion per annum [2]. Stroke incidence rises sharply with age and despite better primary and secondary preventative measures, the total number of strokes is set to rise in the UK [3]. Nevertheless, stroke care in UK is far from ideal: patients having a worse outcome in terms of death and dependency than many other European countries [4-6], at least in part due to differences in care provided [7]. There is also variation in outcome between different localities within the UK [8-11], these local differences being highlighted in the most recent publication of the National Sentinel Stroke Audit in 2009 [12]. These differnces probably arise as a result of substantial variations in how the stroke services are provided across the UK. Examples of such differences are access to neurovascular/neurosurgical service, early supported discharge, and stroke specialist on call rota for thrombolysis. The presence or absence of variations in stroke outcomes as a result of variation in care and how much the observed variations in patients' outcomes including patient reported outcome measure (PROM) are determined by the differences in service delivery have not been examined previously.

We hypothesise that variation in patient outcomes including mortality, length of stay, institutionalisation rate, and patient reported outcomes between care providers can partly be explained by the different ways in which stroke services are delivered. The main objectives of the study are (1) to describe variation in outcomes following stroke and to identify the characteristics of services that are associated with better outcomes after accounting for case mix differences and individual prognostic factors, and (2) to obtain preliminary data to identify sample size and inform future pragmatic real world setting RCTs in the area of health service delivery in stroke.

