### Statistical analysis

Quantitative data will be analysed by multivariate Cox-proportional hazards to examine the relationships between different aspects of health services and time to death, adjusting for prognostic characteristics. Multiple logistic or linear regression models will be constructed as appropriate for dichotomised and continuous outcome variables respectively. T tests for normally distributed data and Mann-Whitney U tests for non-normally distributed data will be used to compare continuous outcomes. Volume-outcome relationships will be investigated. Missing prognostic and EQ-5 D data will be imputed, based on each patient's other prognostic characteristics. Clustering of data by hospital trust will be investigated and, if necessary, taken into account, and intra-class correlation coefficients calculated to inform future research.

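### Complications are counted only during the hospital stay, so time at risk varies with length of stay and services with shorter stays can appear to have fewer complications

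*Protocol article*

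**What the plan says.** Under Outcome measurements, the fourth of six secondary outcomes is "complications during acute and rehab-hospital stay and significant procedures (e.g. aspiration pneumonia, myocardial infarction"). The window is the acute plus rehabilitation hospital stay, with no fixed number of days. The same list makes duration of stay an outcome in its own right: "2) length of acute hospital stay, (3) length of stay in rehabilitation".

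The Background states the hypothesis that "variation in patient outcomes including mortality, length of stay, institutionalisation rate, and patient reported outcomes between care providers can partly be explained" by the way stroke services are delivered. It also illustrates how services vary across the UK: "Examples of such differences are access to neurovascular/neurosurgical service, early supported discharge, and stroke specialist on call rota for thrombolysis".

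For outcomes other than time to death, the Statistical analysis section says "Multiple logistic or linear regression models will be constructed as appropriate for dichotomised and continuous outcome variables respectively". It gives no common observation window and no allowance for time at risk.

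Two further secondary outcomes are not confined to the stay: "5) readmissions, (6) composite cardiovascular events (recurrent TIA/Stroke/Acute Coronary Syndrome, Myocardial infarction"). On data sources, Plan of investigation describes death certificates, hospital episode data and questionnaires, and adds "These data will be counter-checked using discharge coding records, which record each hospital episode".

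**The concern.** A comparison of event risk between services needs the same period of observation in each. Here the period closes when the patient leaves hospital, and time to leaving is one of the things the study expects services to influence. A patient who goes home on day 10 and develops pneumonia on day 14 has no complication under outcome 4. The same patient, in a service that keeps patients for 20 days, has one.

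Adjusting for case mix does not deal with this, because the difference in window comes from the service and not from the patient's prognosis. Adjusting for length of stay is not a clean remedy either, because complications themselves prolong the stay.

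At stake is the reading of one secondary outcome. A service that discharges sooner could be credited with fewer complications when its patients have the same underlying risk.

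**Working it through.** **Inputs.** The documents give the window (acute plus rehabilitation stay) and the expectation that stay varies by provider. They give no complication rate, no lengths of stay and no stated figure for this outcome, so there is nothing to reproduce. All rates and stays below are assumptions. The true hazard is the same in both services throughout, and every patient in a service is given the same stay.

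**Formula.** The probability of a counted complication for a stay of L days is 1 − exp(−H(L)), where H(L) is the cumulative hazard up to day L.

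**Constant hazard, 1% per day: H(L) = 0.01 × L**
- 14 days: 1 − exp(−0.14) = 13.1%. 20 days: 1 − exp(−0.20) = 18.1%. Risk ratio 0.131/0.181 = 0.72.
- 15 days: 1 − exp(−0.15) = 13.9%. 25 days: 1 − exp(−0.25) = 22.1%. Risk ratio 0.63.

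**Declining hazard: H(L) = 0.2 × (1 − exp(−L/τ)), 14 against 20 days**
- τ = 10 days: H = 0.1507 and 0.1729, so risks are 14.0% and 15.9%. Risk ratio 0.88.
- τ = 5 days: H = 0.1878 and 0.1963, so risks are 17.1% and 17.8%. Risk ratio 0.96.

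**Wider check, with the shorter stay half the longer** (7 against 14, 10 against 20 and 14 against 28 days)
- Constant hazards of 0.5% to 2% per day: risk ratios 0.51 to 0.57.
- Hazard starting at 3% per day and declining, H(L) = 0.03 × τ × (1 − exp(−L/τ)): with τ = 5 days, 0.81, 0.89 and 0.95 for the three pairs; with τ = 3 days, 0.92 to 0.99.

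The direction is the same in every case and follows from the definition. The size depends on how steadily complications accrue and how far stays differ.

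**With a common 30-day window.** If every event is ascertained, both services have 1 − exp(−0.30) = 25.9% at 1% per day, and the ratio is 1.00 whatever the stay. That is the best case. Suppose only a fraction q of post-discharge events reaches the hospital record. The counted risk is then 1 − exp(−0.01 × [L + q × (30 − L)]). With q = 0.5 (an assumption), 14 days gives 1 − exp(−0.22) = 19.7% and 20 days gives 1 − exp(−0.25) = 22.1%, a ratio of 0.89. The fixed window moves the ratio from 0.72 towards 1 but does not reach it unless post-discharge events are fully captured.

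**The case against.** The strongest reply is that little depends on this outcome. It is one of six secondary outcomes in an exploratory study that disclaims causal inference. The primary outcome, one-year mortality, has a fixed window. Outcomes 5 and 6 are not limited to the stay: a later myocardial infarction falls under outcome 6, and a pneumonia that brings the patient back to hospital appears as a readmission. The window also runs through rehabilitation, so transfer from acute care to a rehabilitation ward does not close it. Early supported discharge is a Background example and is not among the listed service characteristics. In-stay complications can also be a legitimate measure of inpatient burden, which shorter stays may genuinely reduce.

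Most of this stands, and it limits the weight of the point. It does not remove it. Outcomes 5 and 6 are not added to outcome 4, so a post-discharge pneumonia is at best an unspecified readmission. The hypothesis that length of stay varies with service delivery is the protocol's own, whether or not early supported discharge is analysed. Inpatient burden can be described as such, but it does not show which service has the lower risk of complications.

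A reader might infer three stronger things that the article does not support:
- **That this is the study's main comparison of harm.** Mortality, readmissions and cardiovascular events are compared as well.
- **That the cost analysis inherits the problem.** The Economic evaluation section records resource use over follow-up, including further admissions.
- **That centres with on-site surgery ("availability of vascular surgery on site, neuro-surgery and neuro ITU on site") accumulate events because procedures are scored together with complications.** The two share an item number, but nothing says they are summed. Where a composite is intended, as in outcome 6, the article says so.

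**Conclusion.** The point holds in a conditional form. As written, outcome 4 gives services different times at risk, and with equal true hazards a shorter-stay service can appear to have fewer complications. It would be too strong to say that it will appear safer by any material amount. For assumed stays of 14 and 20 days the risk ratio is 0.72 if the hazard is constant and 0.88 to 0.96 if it declines with a time constant of 10 or 5 days. It is close to 1 if nearly all complications fall in the first days. These figures assume the same hazard before and after discharge and identical patients. The documents supply neither complication rates nor stays that would narrow the range. The definition is stated in the article itself, so this is not a detail left to an analysis plan. The consequence is confined to one secondary outcome.

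**What to change.** For comparisons between services, define outcome 4 as the first occurrence of each listed complication within a fixed window from admission that is the same for all patients, for example 30 days with 90 days as a check. Count events in the index stay or coded at a readmission. Keep complications during the stay as a descriptive item, reported alongside length of stay.

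The cost is small: a change of definition, plus linking complications coded at readmission to the index admission. Case records, hospital episode data and readmissions are already to be collected, and one year of follow-up is planned.

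The limitation should be stated in the plan. Complications managed only in the community are still missed, so some bias in favour of shorter-stay services remains.
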